## **6.2 Statistical Analysis**

Baseline data are described as mean with standard deviation (SD), median, and range in case of continuous variables and as frequencies with percentages in case of categorical variables.

All statistical analyses will be conducted with SPSS software, version 22.0 (SPSS Inc., Chicago, IL, USA). A two-tailed P value less than 0.05 is considered to be statistically significant.

### **● Baseline characters**

Calculate the mean with SD, median, maximum, and minimum of gender, ECOG score and other qualitative variables. List the frequency and percentage of age, height, weight and other quantitative variables. Categorical variables are assessed using the X2 test or Fisher's exact test, and continuous variables are compared using Student's t test or the Mann-Whitney U test.

### **● Efficacy**

#### **- Primary Efficacy Measures**

Calculate the R0 resection rate with 95% confidence interval (CI).

#### **- Secondary Efficacy Measures**

Calculate the pathological/radiologic response rate with 95% CI. The Kaplan-Meier method is used to analyze overall survival (OS) and disease-free survival (DSS), and the differences are assessed with log-rank tests.

### **● Safety**

These results mainly use description analysis. List all the AEs in this study. List the frequency and percentage of postoperative morbidity, mortality, readmission, and reoperation and the median with range of blood loss, time to food intake, and postoperative hospital days.

## **7. Data management**

### **7.1 Filling and Modifying**

An independent data monitoring committee is responsible for data filling and management. To ensure the accuracy, two data administrators enter the data and then proofread. If there are any questions in the CRF, the data administrators will fill in the DRQ and send a query to the researchers through the clinical monitor. The researchers should make a answer and return as soon as possible. Data modification, confirmation and entry will be done according to the response. DRQ can be sent again if necessary.

### **7.2 Data Lock**

After data review and confirmation, the database will be locked by the principle investigator, sponsor, and statistical analyst. The locked data file can be no longer changed.

## **8. Quality Control and Assurance**

Researchers must be experienced clinical physicians and work under the guidance of senior professionals.

The clinical ward must meet the standardized requirements to ensure that the rescue equipment is complete.

It is recommended that drug administration should be performed by professional nursing staff to ensure good compliance of participants.

Research centers must strictly follow the study protocol and enter the CRF truthfully.

The supervisor should supervise this trial according to the standard operating procedures, and confirm that all data and reports are correct and complete, all CRFs are entered correctly.

## **9. Ethics, regulations and administrative principles**

### **9.1 Local regulations / Helsinki Declaration**

The researchers should ensure the implementation of this study in accordance with the study protocol and in compliance with the Declaration of

Helsinki, as well as domestic and international ethical guiding principles and applicable regulatory requirements. The present study must strictly follow the "Guideline for Good Clinical Practice" ICH Tripartite Guideline (January 1997), or local law, whichever is more stringent.

## **9.2 Informed Consent**

An unconditional prerequisite for subjects to participate in this study is his/her written informed consent. The written informed consent of subjects participating in this study must be given before study-related activities are conducted.

Therefore, before obtaining informed consent, the investigators must provide sufficient information to the subjects. In order to obtain the informed consent, the investigators will provide the information page to subjects, and the information required to comply with the applicable regulatory requirements. While providing written information, the investigators will orally inform the subjects of all the relevant circumstances of this study. In this process, the information must be fully and easily understood by non-professionals, so that they can sign the informed consent form according to their own will on the basis of their full understanding of this study.

The informed consent form must be signed and dated personally by the subjects and investigators. All subjects will be asked to sign the informed consent form to prove that they agree to participate in the study. The signed informed consent form should be kept at the research center where the investigator is located and must be properly safe kept for future review at any time during audit and inspection throughout the inspection period. Before participating in the study, the subjects should provide a copy of signed and dated informed consent form.

At any time, if important new information becomes available that may be related to the consent of the subjects, the investigators will revise the information pages and any other written information which must be submitted to the IEC/IRB for review and approval. The revised information approved will be provided to each subject participating the study. The researchers will explain the changes made to the previous version of ICF to the subjects.

## **9.3 Independent Ethics Committee or Institutional Review Committee**

Before the study begins, all research centers should submit the study

protocol and relevant documents (ICF, CRF, and other documents that may be required) to the Independent Ethics Committee (IEC)/ Institutional Review Board (IRB). The study can only start after obtaining the approval from the IEC/IRB. Any amendment of the study protocol must be submitted to the IEC/IRB first in accordance with local laws and regulations.

#### **9.5 Record Keeping**

Researchers should arrange for the storage of the research files until the end of the study. Additionally, researchers should adhere to specific local regulations/guidelines in record keeping.

Unless otherwise stated in the agreement, it is recommended to keep the research files for at least five years after completion or interruption of the study.

#### **9.6 Interruption of the Study**

The principal investigator can decide to discontinue this study at any time and for any reason; the decision to discontinue the study will be communicated in writing to the participating researchers and Jiangsu Hengrui Pharmaceutical Co., Ltd.

Similarly, if another researchers decide to withdraw from the study, they must notify the company in writing.

If applicable, notify the IRB health regulatory authorities in accordance with local regulations.

### **10. Protocol Modification**

Any revisions to the protocol will be recorded in a written revision and

signed by researchers and sponsor. A signed, revised version will be attached to the protocol. A revised version should be submitted in accordance with local regulations.

## **11. Use of Research Results**

### **11.1 Ownership**

The use of data should be permitted by the principle investigator and Jiangsu Hengrui Pharmaceutical Co., Ltd.

The principle investigator has full access to the final data to perform appropriate academic analysis and to report of the research results.

### **11.2 Publication**

All participating researchers fully authorize the principle investigator to publish the research results for the first time. Other publication is not permitted until the first publication. Any subsequent publication (including sub-analysis) must be approved by the principle investigator and cited for the first publication of this study.

After notifying the company in advance (for internal review and comments), the principle investigator will make the final decision on the publication of any manuscript/abstract/presentation. All manuscript/abstract/presentation must be submitted to the sponsor for internal review at least 45 days before submission. Jiangsu Hengrui Pharmaceutical Co., Ltd. may require the name of the sponsor and/or the names of one or more employees of the sponsor to be listed or not listed in this publication.

Jiangsu Hengrui Pharmaceutical Co., Ltd. may delay publication or transmission for a limited period of time in order to protect the confidentiality or ownership of any information contained therein.

504

505 **References**

506 [1] Bray F, Ferlay J, Soerjomataram I, et al. Global cancer statistics 2018:  
507 GLOBOCAN estimates of incidence and mortality worldwide for 36 cancers in  
508 185 countries. *CA Cancer J Clin.* 2018; 68: 394-424.

509 [2] Pyo Jeung Hui, Lee Hyuk, Min Byung-Hoon, et al. Long-Term Outcome of  
510 Endoscopic Resection vs. Surgery for Early Gastric Cancer: A  
511 Non-inferiority-Matched Cohort Study. *Am. J. Gastroenterol.* 2016; 111: 240-9.

512 [3] Songun I, Putter H, Kranenbarg EM, et al. Surgical treatment of gastric  
513 cancer: 15-year follow-up results of the randomised nationwide Dutch D1D2 trial.  
514 *Lancet Oncol.* 2010 ;11: 439–449.

515 [4] Cunningham D, Allum WH, Stenning SP, et al. Perioperative chemotherapy  
516 versus surgery alone for resectable gastroesophageal cancer. *N Engl J Med.*  
517 2006; 355: 11–20.

518 [5] National Comprehensive Cancer Network: NCCN Clinical Practice  
519 Guidelines in Oncology: Gastric Cancer (version 2.2015).

520 [6] Okines AF, Norman AR, McCloud P, et al. Meta-analysis of the REAL-2 and  
521 ML17032 trials: evaluating capecitabine-based combination chemotherapy and  
522 infused 5-fluorouracil-based combination chemotherapy for the treatment of  
523 advanced oesophagogastric cancer. *Ann Oncol.* 2009; 20: 1529–1534.

524 [7] Yamada Y, Higuchi K, Nishikawa K, et al. Phase III study comparing  

N0 No regional lymph node metastasis

N1 One to two regional lymph nodes are positive

N2 Three to six regional lymph nodes are positive

N3 Seven or more regional lymph nodes are positive

N3a Seven to fifteen regional lymph nodes are positive

N3b Fifteen or more regional lymph nodes are positive

- Definition of Distant Metastasis (M)

M0 No distant metastasis

M1 Distant metastasis

605

| GROUP                         | T     | CLINICAL |    |
|-------------------------------|-------|----------|----|
|                               |       | N        | M  |
|  0    | Tis   | N0       | M0 |
|  IA   | T1    | N0       | M0 |
|  IB   | T2    | N0       | M0 |
|  IIA  | T1    | N1       | M0 |
|                               | T3    | N0       | M0 |
|                               | T2    | N1       | M0 |
|  IIB  | T1    | N2       | M0 |
|                               | T4a   | N0       | M0 |
|                               | T3    | N1       | M0 |
|                               | T2    | N2       | M0 |
|  IIIA | T1    | N3       | M0 |
|                               | T4a   | N1       | M0 |
|                               | T3    | N2       | M0 |
|  IIIB | T2    | N3       | M0 |
|                               | T4b   | N0       | M0 |
|                               | T4b   | N1       | M0 |
|                               | T4a   | N2       | M0 |
|  IIIC | T3    | N3       | M0 |
|                               | T4b   | N2       | M0 |
|                               | T4b   | N3       | M0 |
|  IV   | T4a   | N3       | M0 |
|                               | Any T | Any N    | M1 |

| GROUP                         | T     | PATHOLOGIC |    |
|-------------------------------|-------|------------|----|
|                               |       | N          | M  |
|  0    | Tis   | N0         | M0 |
|  IA   | T1    | N0         | M0 |
|  IB   | T2    | N0         | M0 |
|  IIA  | T1    | N1         | M0 |
|                               | T3    | N0         | M0 |
|                               | T2    | N1         | M0 |
|  IIB  | T1    | N2         | M0 |
|                               | T4a   | N0         | M0 |
|                               | T3    | N1         | M0 |
|                               | T2    | N2         | M0 |
|  IIIA | T1    | N3         | M0 |
|                               | T4a   | N1         | M0 |
|                               | T3    | N2         | M0 |
|  IIIB | T2    | N3         | M0 |
|                               | T4b   | N0         | M0 |
|                               | T4b   | N1         | M0 |
|                               | T4a   | N2         | M0 |
|  IIIC | T3    | N3         | M0 |
|                               | T4b   | N2         | M0 |
|                               | T4b   | N3         | M0 |
|  IV   | T4a   | N3         | M0 |
|                               | Any T | Any N      | M1 |

606

607 ● Histologic Grade (G)

608 Gx Grade cannot be assessed

609 G1 Well differentiated

610 G2 Moderately differentiated

611 G3 Poorly differentiated

612

## **Appendix 3**

### **Response Evaluation Criteria in Solid Tumors (RECIST) Version 1.1**

#### **Response criteria**

This section provides the definitions of the criteria used to determine objective tumour response for target lesions.

- **Evaluation of target lesions**

**Complete Response (CR):** Disappearance of all target lesions. Any pathological lymph nodes (whether target or non-target) must have reduction in short axis to <10 mm.

**Partial Response (PR):** At least a 30% decrease in the sum of diameters of target lesions, taking as reference the baseline sum diameters.

**Progressive Disease (PD):** At least a 20% increase in the sum of diameters of target lesions, taking as reference the smallest sum on study (this includes the baseline sum if that is the smallest on study). In addition to the relative increase of 20%, the sum must also demonstrate an absolute increase of at least 5 mm. (Note: the appearance of one or more new lesions is also considered progression).

**Stable Disease (SD):** Neither sufficient shrinkage to qualify for PR nor sufficient increase to qualify for PD, taking as reference the smallest sum diameters while on study.

- **Evaluation of non-target lesions**

This section provides the definitions of the criteria used to determine the tumour response for the group of non-target lesions.

While some non-target lesions may actually be measurable, they need not be measured and instead should be assessed only qualitatively at the time points specified in the protocol.

**Complete Response (CR):** Disappearance of all non-target lesions and normalisation of tumour marker level. All lymph nodes must be non-pathological in size (<10 mm short axis).

**Non-CR/Non-PD:** Persistence of one or more non-target lesion(s) and/or

645 maintenance of tumour marker level above the normal limits.

646 Progressive Disease (PD): Unequivocal progression (see comments below) of  
647 existing non-target lesions. (Note: the appearance of one or more new lesions is  
648 also considered progression).

649

## **Appendix 4**

### **ECOG PS score**

According to the simplified performance status score scale developed by the ECOG, the patients' performance status can be classified into 6 levels, namely 0-5, as follows:

0: Fully active, able to carry on all pre-disease performance without restriction;

1: Restricted in physically strenuous activity but ambulatory and able to carry out work of a light or sedentary nature, e.g., light housework, office work;

2: Ambulatory and capable of all self-care but unable to carry out any work activities. Up and about more than 50% of waking hours;

3: Capable of only limited self-care, confined to bed or chair more than 50% of waking hours;

4: Completely disabled. Cannot carry on any self-care. In total, confined to bed or chair;

5: Dead.

Patients at levels 3, 4 and 5 are generally considered to be unsuitable for surgical treatment or chemotherapy.

## Appendix 5

### Dose Reductions and Interruption

Toxicities in the preoperative treatment are evaluated according to the National Cancer Institute-Common Terminology Criteria for Adverse Events, version 4.0. The reason for dose reductions or delay, supportive treatment performed by clinicians and outcomes will be recorded on the CRF.

#### 1. General Considerations for Dose Adjustment

- For AEs present at baseline, the dose can be adjusted according to the change in grades. For example, if grade 1 weakness at baseline progresses to grade 2 during treatment, the dose can be adjusted as the presence of a grade 1 toxicity.
- There is no need to reduce the dose or discontinue the treatment with the presence of the toxicities which are unlikely to develop into severe events (such as hair loss, appetite changes, etc.) occur. Additionally, there is no need to reduce the dose or discontinue the treatment with the presence of anemia (non-hemolytic) because it can be improved by transfusion.
- When different grades of toxicities occur simultaneously, dose reduction should be taken according to the most severe of them.
- During treatment, if all study drugs need to be delayed or discontinued for more than six weeks, the patient will withdraw from the study. If only one drug is discontinued, the study still proceeds.
- If a patient develop a grade 3 or higher non-hematological AE, it can be discussed with the sponsor whether to reduce the dose or not.

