#### 2. Principles for Dose Adjustment and Interruption

When a grade 3/4 hematological/non-hematological AE occurs, the researcher should judge its relation to targeted agent/chemotherapy drugs: if the toxicity is related to the targeted agent, reduce the dose of apatinib to 250 mg qd; if the toxicity is related to chemotherapy drugs, reduce the dose or discontinue the treatment of Tigio or oxaliplatin. If the researcher cannot determine the relation between the toxicity and the drugs, it is recommended to discontinue apatinib first and observe for 24 hours. If the toxicity does not resolved, discontinue the chemotherapy drugs.

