#### 3.2 Principles for Dose Adjustment and Interruption

- Dose reductions are allowed in the presence of grade 3 treatment-related toxicities.
- Among non-hematological toxicities, there is no need to reduce the dose or discontinue the treatment in the presence of manageable nausea, vomiting, hair loss, fever with a defined cause (such as infection or tumor), and grade 3/4 elevated alkaline phosphatase (AKP).
- Dose reductions are allowed up to twice. Treatment interruption is allowed for no more than 14 days (cumulatively) and no more than two times in each cycle. Dose re-escalation is not permitted.
- Treatment interruption is first performed during each cycle. Then dose reduction can be performed when the subject is still intolerant.
- Special AEs: Once hypertension crisis, cerebral hemorrhage, grade 2 or higher pulmonary hemorrhage, grade 3 or higher other bleeding, arterial thrombosis, grade 4 venous thrombosis, leukoencephalopathy syndrome, or gastrointestinal perforation occurs, immediately discontinue the treatment and perform active symptomatic treatment; the subject then withdraw from the study.

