#### Principles for Dose Adjustment of Apatinib

| Classification | Grade | Regulations for Dose Adjustment                                                                                                                                                                               |
|----------------|-------|---------------------------------------------------------------------------------------------------------------------------------------------------------------------------------------------------------------|
| Hematologic    | 1-2   | Maintain the original dose                                                                                                                                                                                    |
|                | 3     | Discontinue the treatment until the toxicity $\leq$ grade 2, then continue the treatment at the original dose. If a grade 3 or higher toxicity recurs, continue the treatment after one-level dose reduction. |
|                | 4     | Discontinue the treatment until the toxicity $\leq$ grade 2, then continue the treatment after one-level dose reduction.                                                                                      |
| Nonhematologic | 1-2   | Maintain the original dose                                                                                                                                                                                    |
|                | 3     | Discontinue the treatment until the toxicity $\leq$ grade 1, then continue the treatment at the original dose. If a grade 3 or higher toxicity recurs, continue the treatment after one-level dose reduction. |

|  |   |                                                                                                                          |
|--|---|--------------------------------------------------------------------------------------------------------------------------|
|  | 4 | Discontinue the treatment until the toxicity $\leq$ grade 1, then continue the treatment after one-level dose reduction. |
|--|---|--------------------------------------------------------------------------------------------------------------------------|

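### Appendix 5 gives inconsistent instructions for grade 3/4 non-haemolytic anaemia, and nothing says which passage prevails

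*Protocol*

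**What the plan says.** All the relevant text is in Appendix 5 of the protocol.

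- **Section 1, General Considerations for Dose Adjustment:** there is "no need to reduce the dose or discontinue the treatment with the presence of anemia (non-hemolytic"), the reason given being that transfusion can improve it. Haemolysis is the only carve-out; no grade limit is set.
- **Section 2, Principles for Dose Adjustment and Interruption:** it opens "When a grade 3/4 hematological/non-hematological AE occurs" and asks the researcher to judge the relation to the drugs. Toxicity related to the targeted agent leads to apatinib 250 mg daily. Toxicity related to chemotherapy leads to reducing or stopping S-1 or oxaliplatin. If the relation cannot be determined, apatinib is stopped first, and chemotherapy follows if the toxicity has not resolved after 24 hours.
- **Section 3.2 (apatinib):** its list of exemptions begins "Among non-hematological toxicities, there is no need to reduce the dose" and does not mention anaemia. A separate list of special events that end treatment includes "grade 3 or higher other bleeding".
- **Apatinib table, haematologic rows:** grade 1–2 keeps the dose. Grade 3 reads "Discontinue the treatment until the toxicity $\leq$ grade 2, then continue the treatment at the original dose", with a one-level reduction on recurrence. Grade 4 reads "Discontinue the treatment until the toxicity $\leq$ grade 2, then continue the treatment after one-level dose reduction".
- **Section 4 (S-1/oxaliplatin):** reductions are permitted from grade 3 haematologic toxicity, with no mention of anaemia.

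**The concern.** Anaemia is a haematologic toxicity, so at grade 3 or 4 it falls under the apatinib table and section 2 as well as under the exemption in section 1. One passage treats action as unnecessary and two prescribe it. Blood counts are taken on day 7 of cycle 1 and on days 1 and 7 of cycles 2–5 (section 4.2 of the protocol body), so sites will face this decision if such anaemia occurs.

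Three things depend on the reading:

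- **Exposure.** Section 3.2 of Appendix 5 allows two apatinib reductions at most, bars re-escalation, and caps interruption at 14 days per cycle. A reduction made under one reading cannot be undone.
- **Per-protocol status.** Section 3.2.3 of the protocol body rejects patients who do not take medication as prescribed, and section 6.2 requires protocol compliance for the per-protocol set. Efficacy is analysed in that set as well as in the full analysis set.
- **Recorded dose modifications.** Their frequency would partly reflect which paragraph a site read.

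**Working it through.** The documents give no figure to reproduce. The check sets the passages side by side for non-haemolytic anaemia.

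| Situation | Section 1 | Apatinib table | Section 2 | Consistent? |
|---|---|---|---|---|
| Grade 1–2 | no change needed | keep dose | not addressed | yes |
| Grade 3, related to apatinib | no change needed | interrupt, resume at same dose; reduce if it recurs | reduce to 250 mg daily | no |
| Grade 4, related to apatinib | no change needed | interrupt, resume one level lower | reduce to 250 mg daily | no |
| Grade 3/4, related to chemotherapy | no change needed | interrupt apatinib | reduce or stop S-1 or oxaliplatin | no |
| Grade 3/4, relation undeterminable | no change needed | interrupt apatinib | stop apatinib, then chemotherapy if unresolved | no |
| Grade 3/4, judged unrelated | no change needed | interrupt apatinib, if the rows apply regardless of cause | no action specified | unclear |

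The last row is unclear because the table does not mention attribution, while section 3.2 ties apatinib dose reductions to treatment-related toxicity.

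**Precedence.** Neither section 1, section 2 nor the table refers to the others on anaemia, and none states an order. Section 1 also says that, of simultaneous toxicities, the most severe governs dose reduction. That ranks toxicities, not conflicting instructions for one toxicity.

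**Section 4.** Its wording permits reduction without requiring it, so it does not contradict section 1 outright. It has the same silence on anaemia and should be aligned.

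**Bleeding.** The stop in section 3.2 is triggered by the bleeding event, whatever the haemoglobin. Section 1 exempts anaemia only, so it cancels nothing there. Blood-loss anaemia is non-haemolytic and therefore falls within the conflict in the table above, like any other non-haemolytic anaemia. Where no special-event stop applies, only the conflicting passages remain.

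**Exposure for one patient over a 21-day cycle, starting from 500 mg daily:**

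- Unchanged: 500 × 21 = 10,500 mg.
- Reduced one level for the whole cycle: 250 × 21 = 5,250 mg, or 50%.
- Interrupted for the full 14 days allowed, otherwise 500 mg: 500 × 7 = 3,500 mg, or about 33%.

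**Number of patients.** The documents give no anaemia rate. Assuming 5–15% of 50 patients reach grade 3/4: 0.05 × 50 = 2.5 and 0.15 × 50 = 7.5. The contradiction does not depend on this range.

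**The case against.** The best defence is that section 1 is a specific exception to general rules. It names one toxicity and gives a reason, transfusion. Appendix 5 also tends to keep exceptions in the text and leave the table bare: the non-haematologic rows do not mention the exemptions listed in section 3.2 just above them. The table's silence is therefore weak evidence by itself. This reading is plausible, but the text does not settle it. Section 1 is headed as general, whereas the table is specific to apatinib. Section 3.2 repeats the hair-loss exemption from section 1 but not the anaemia one, and confines its list to non-haematological toxicities.

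A second defence is that saying there is no need to act is permissive. That is correct: a reader might infer that sites are forbidden to hold or reduce, and the text does not say so. A site that interrupts under the table breaches nothing in section 1. The reverse does not hold, because a site that continues in reliance on section 1 departs from a directive row of the table.

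Third, section 2 does not act on every grade 3/4 event; it specifies nothing for an event judged unrelated to the drugs. This stands and narrows the conflict with section 2.

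Finally, a reader might infer that blood-loss anaemia receives opposite orders, continue under section 1 and stop under section 3.2. The documents do not support that, because the stop acts on the bleeding itself and the anaemia exemption leaves it intact.

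**Conclusion.** The inconsistency is real and confined to non-haemolytic anaemia of grade 3 or 4. Section 1 conflicts with the haematologic rows of the apatinib table, and with section 2 where the event is drug-related or cannot be attributed. Grade 1–2 anaemia and the bleeding stop are not part of it.

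Severity is low. Full-analysis-set membership depends on having received at least one neoadjuvant cycle and is unaffected by later dose handling. No distortion of the R0 resection rate has been shown. The consequences are site-dependent apatinib exposure that cannot be reversed after a reduction, and uncertain per-protocol status for the patients concerned. Their number is unknown; 2.5 to 7.5 of 50 rests wholly on an assumed rate. The conclusion itself rests only on the wording of Appendix 5 and the absence of any statement of precedence.

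**What to change.** Reconcile section 1, section 2 and the haematologic rows of the apatinib table in Appendix 5, and align section 4 for S-1 and oxaliplatin. State whether the anaemia exemption overrides the haematologic rules and, if so, for which grades, which causes (including blood loss) and which drugs. The clinical choice belongs to the sponsor's clinical team; this review takes no position on it.

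The cost is one clarified sentence in Appendix 5, ideally with a cross-reference at the table, processed as a protocol revision under section 10. No change to sample size, endpoints or analysis is needed.
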